#### Relevant concomitant care permitted or prohibited during the trial

Relevant concomitant care and interventions permitted or prohibited during the trial have been carefully considered following the trial’s guidelines. Participants will be allowed to continue any medication or treatment for chronic pain they are currently receiving but will be asked to refrain from beginning any new treatments or therapies during the trial. However, participants will be encouraged to continue their regular daily activities and exercise regimen. To ensure the validity of the intervention, participants will be asked to refrain from engaging in any mindfulness or meditation practices other than those provided by the study during the trial. These measures will contribute to the overall scientific rigor of the trial and ensure that the effects of the mindfulness practice intervention can be accurately assessed.

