## Introduction

### The burden of parents of children with ASD

Autism spectrum disorder (ASD) is defined as a group of complex neurodevelopmental disorders, including autism, Asperger syndrome, pervasive developmental disorder not otherwise specified (PDD-NOS), and other relevant symptoms and conditions [1]. According to a most updated systematic review, the prevalence of ASD among children aged 4 and 8 years in the United States was 1.70 and 1.85 percent, respectively, while the prevalence in Europe ranged from 0.38 to 1.5 percent [2]. Another meta-analysis reported a pooled prevalence of ASD of 0.27% (95% CI: 0.19–0.35%) in Mainland China, Hong Kong, and Taiwan [3]. The General Household Survey in Hong Kong conducted in 2019 and 2020 by the Census and Statistic Department reported that the prevalence rate of autistic spectrum disorder (ASD) among the local population below 15 is estimated at around 1.4% [4].

To take care of children with ASD, parents may suffer from different hardships. A most recent meta-analysis reported that around 31% (95% CI: 24–38%) and 33% (95% CI: 20–48%) of parents of children with ASD suffer from depression and anxiety, respectively [5]. In the Chinese context, where special education service organizations are limited [6], parents have to make much more effort to educate, coach, and support their children and prepare the independent living of their children with ASD compared with other parents [7]. Families of children with ASD may experience more parenting stress than families of children with other disabilities [8]. Parental psychological distress may also reduce the effectiveness of early teaching interventions on their children and increase children’s behavior problems [9].

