## Methods

### Trial design

This research adopts a parallel-armed, randomized controlled trial (RCT) design. The intervention group will receive a combination of (1) a time-based system-triggered EMA, which will collect participants’ sources and status of depression, anxiety, and depression in daily life; (2) EMI-delivered MBI, and (3) a follow-up survey of long-term effects of EMI/A-MBI. The participants will complete a baseline questionnaire and then participate in EMI via a smartphone application (App) for eight consecutive weeks and receive the daily exercise prompts. The EMA will include questions about self-reported depression, anxiety, and depression. After the 8-week EMI/A-MBI, the participants will be invited to complete a post-experimental survey with similar questions in the baseline questionnaire. Two months after completing the EMI/A-MBI, participants will be contacted to complete a telephone follow-up survey with similar questions in the baseline questionnaire. The control group will receive the longitudinal survey exactly the same as the intervention group and 8-week mindfulness-based short messages sent by the research team on a daily basis. The messages will contain audio-based instructions for mindfulness-based practice, which will be the same as the intervention group. The SPIRIT schedule of enrolment, interventions, and assessments can be found in Fig 1 and the flowchart of the design can be found in Fig 2. (The SPIRIT checklist can be found in S1 File).

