#### Participants

The inclusion criteria will comprise (1) parents of children with ASD (children aged between 6–18 and diagnosed with different functional levels of ASD by certified psychologists); (2) own a mobile smartphone with internet access; (3) will stay in Hong Kong during the 8-week EMI/A-MBI study period, and (4) able to read and write in Chinese. The exclusion criteria will include (1) parents diagnosed with depression, anxiety, and stress disorder by certified doctors; and (2) parents who do not live together with their children with ASD on a daily basis.

After participants enrol online or are recruited offline from community centers, the research assistant (RA) will explain the study objectives and procedure to participants and get informed consent from all participants.

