#### The explanation for the choice of comparators

As mindfulness-based intervention has been proven effective for parents of children with autism, we will involve the components of mindfulness in both the intervention and control groups. Therefore, any extra effects incurred in the intervention group can be attributed to the benefits of using EMI and EMA.

The intervention will be discontinued or modified when participants report feeling more psychological distress while practicing mindfulness-based intervention.

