#### Adverse event reporting and harms

The proposed mindfulness-based intervention is a behavioural approach without invasive procedures and medication; no side effects or adverse outcomes will be expected. All participants will be asked at telephone follow-up by the research assistant if they encounter difficulties using the smartphone app. If so, and the participant agrees, the research assistant will refer these participants to the specialists.

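### The request to begin no new treatment has no exception for clinical need and is worded around chronic pain, and the plan to record outside support is unclear on arm and scope

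*Protocol article*

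**What the plan says.** The section on concomitant care has two sentences that matter here. On existing care: "Participants will be allowed to continue any medication or treatment for chronic pain they are currently receiving". On new care, participants "will be asked to refrain from beginning any new treatments or therapies during the trial". Neither sentence names an arm, so both apply to all 670 planned participants. A further sentence asks them to avoid mindfulness or meditation from outside the study.

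Three other places bear on what happens to a participant who worsens:

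- Participants: the exclusion covers "parents diagnosed with depression, anxiety, and stress disorder by certified doctors", so parents without a diagnosis can enrol whatever their symptoms.
- The explanation for the choice of comparators: "The intervention will be discontinued or modified when participants report feeling more psychological distress while practicing mindfulness-based intervention".
- Adverse event reporting and harms: "All participants will be asked at telephone follow-up by the research assistant if they encounter difficulties using the smartphone app"; if so, and with the participant's agreement, "the research assistant will refer these participants to the specialists".

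On recording outside care, the limitations paragraph of the Discussion says that control participants may look for help elsewhere, that this could make the group difference hard to identify, and that data on their involvement in other projects will be collected to deal with it. Under Trial design, "The control group will receive the longitudinal survey exactly the same as the intervention group".

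**The concern.** The trial enrols a group in which a need for new care is foreseeable. The Introduction cites pooled figures of about 31% (95% CI 24–38%) and 33% (20–48%) "of parents of children with ASD suffer from depression and anxiety, respectively". The primary outcome is psychological distress on the DASS. A rule that asks people to start nothing new, with no exception, therefore reaches the very care that a worsening parent would need.

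Two things are at stake. The first is participant protection: a parent or research assistant who follows the text as written has no statement that starting necessary care is acceptable and compatible with staying in the trial. The second is interpretation. The comparator section attributes any additional benefit in the intervention arm to EMI and EMA. The Discussion itself names outside support as a threat to identifying the group difference, so the record of outside care ought to be one that can be compared between arms.

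**Working it through.** No figure in the plan depends on this point, so the check sets the passages side by side.

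**1. Does any visible passage supply the missing exception?**

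- The comparator section foresees rising distress, but the action it states is on the study intervention. It says nothing about access to outside care.
- The app's virtual counselor (Intervention description) responds to distress ratings by recommending mindfulness practices.
- The referral to specialists is triggered by difficulty with the app, not by distress. It is asked at the telephone follow-up, which Follow-up and incentive places two months after the intervention ends.
- The ethics section gives a right to withdraw at any time without penalty. That lets a participant leave; it does not say that one may start treatment and remain.

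None of the four is an exception to the request.

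**2. Does the chronic-pain wording fit?** Eligibility concerns parents of children with ASD. The outcomes are the DASS, life satisfaction and empowerment. Chronic pain is neither an eligibility item nor an outcome. If the permitted-care sentence is read broadly, so that every current medication is allowed, existing counselling or psychological therapy is still not clearly covered. No sentence forbids it either; the text simply does not address the care most relevant to a distress outcome.

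**3. How long does the request last?** The text says only that it holds during the trial.

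- Intervention period only: 8 weeks = 56 days.
- Including the 2-month follow-up, taking two months as about 61 days: (56 + 61) / 7 = 16.7, so about 17 weeks.

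The section does not say which is meant.

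**4. What would the outside-support data show?** In the Discussion, the natural antecedent of the pronoun is the control group, named in the sentence before. Other projects is also narrower than the services and support just mentioned, and does not plainly include medication or counselling. Against that, Trial design gives both arms the same survey, so an item placed there would be answered by both. The Outcomes section lists demographics, distress and well-being, and the named model covariates are baseline DASS and demographic variables; neither mentions outside care. The text therefore leaves both the arm and the scope open.

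**5. Can the effect on the group contrast be sized?** No. The article gives neither the expected uptake of outside care by arm nor its effect on the DASS. Any figure for diluted effect or lost power would rest wholly on assumed values.

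**The case against.** The strongest reply has four parts.

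- **It is a request, not a ban.** This stands. No passage makes starting care a ground for removal, withdrawal carries no penalty, and the Discussion expects some controls to seek help and responds by recording it. A reader might infer that the trial prohibits treatment or removes those who start it; the article does not say so. What remains is that the only stated guidance points away from starting care.
- **The full documents may cover it.** The approved protocol and consent form are supplementary files and the measurement figure is not shown. Any of them could hold an exemption or a concomitant-care item for both arms. This stands as a limit: the point concerns what the article states. It would not repair the chronic-pain phrase or the unqualified request in the article.
- **The outside-support data may reach both arms.** This also stands. A reader might infer that the plan is unable to show whether outside care differed between arms. Because both arms complete the same survey, that goes too far; unclear is as much as the wording supports.
- **The comparison is valid anyway.** Correct. Care begun after randomisation is part of the effect of assignment, and randomisation protects that contrast. A reader might infer bias from unequal outside care, but nothing in the article shows an imbalance.

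It is also tempting to multiply the Introduction's prevalence figures by the sample size to count the people affected. That would mislead, because parents with a diagnosis are excluded and the article does not say how many symptomatic, undiagnosed parents remain.

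**Conclusion.** The point holds as a minor one. The concomitant-care section asks all participants to begin no new treatment, states no exception for clinical need, and carries a chronic-pain phrase that does not belong to this trial. The provisions on stopping or modifying the intervention and on referral for app difficulties do not fill the gap. The Discussion's plan for outside support is at best unclear on which arm and what care it covers.

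The consequence is weaker participant protection and weaker support for attributing any extra effect to EMI and EMA. The validity of the intention-to-treat contrast is not in question, and its sensitivity to outside care cannot be estimated from the article. The conclusion assumes that the article's wording reflects the rule staff and participants will follow. If the full protocol or consent form already contains the exemption and a question for both arms, only the article's wording needs correcting.

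**What to change.** 1. In the concomitant-care section, state that care a participant or clinician judges necessary is exempt from the request and compatible with staying in the trial. Say whether the request covers the 8 weeks only or also the follow-up.
2. Replace the chronic-pain phrase with wording that allows existing psychological or psychiatric care and medication to continue.
3. Reword the Discussion sentence so that one identical question goes to both arms on the common survey at post-test and 2-month follow-up: any new psychological treatment, medication, counselling or other programme, with start date. Report the answers by arm and keep all participants in the intention-to-treat analysis.

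The cost is a wording amendment, carried into the consent form if that repeats the request, and one extra item on a survey both arms already complete. An explicit exemption may slightly raise the use of outside care, but it would then be recorded. Design, sample size and primary analysis are unchanged.

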#### Outcomes

At baseline, post-test, and follow-up survey, the questionnaire contains the same questions concerning demographic information (will only ask at baseline). Psychological distress and mental well-being will be administered to participants in both intervention and control groups. Demographic information, including parent and children’s gender, parent and children’s age, years of children diagnosed with ASD, number of children living in the same household, family monthly income, parents’ education level, parents’ employment status, and average time spent with children daily. The primary outcome will be participants’ psychological distress measured by the depression anxiety stress scale. The secondary outcomes will include participants’ subjective well-being, measured by the satisfaction with life scale, and level of resilience, measured by the psychological empowerment scale. (Detailed measurement information can be found in Fig 3)

**Fig 3 pone.0291168.g003:**
[figure not shown]
Summarizations of measurements.

*The cognitive Appraisal of Health Scale* will be used to measure participants’ cognitive appraisal of daily life events. This scale includes 28 items rated from 1 strongly disagree to 5 strongly agree. This scale was developed based on the transactional theory of stress and coping and thus consists of subscales of primary appraisal (threat, challenge, harm/loss, and benign/irrelevant) and secondary appraisal. The internal consistencies were all greater than 0.70 [46].

*The Five Facet Mindfulness Questionnaire (FFMQ)-short version* [47, 48] will be used to measure participants’ level of mindfulness before and after practicing. It includes 15 items measuring the five facets of mindfulness: observing, describing, acting with awareness, non-judging of inner experience, and non-reactivity to inner experience. This scale was further validated [49] and yielded good convergent validity and internal consistency [49].

Parents’ psychological distress will be assessed in the domains of depression, anxiety, stress, and mental well-being, indicating participants’ life satisfaction and empowerment.

*The Depression Anxiety Stress Scale (DASS)* [50] is a self-report questionnaire that measures the emotional states of depression, anxiety, and stress. This scale contains 21 questions rated from 0 (did not apply to me at all) to 3 (applied to me very much, or most of the time). There were seven questions for each sub-scale of stress, depression, and anxiety [51]. This scale was reliable (alpha = 0.96 and 0.80 for the depression and anxiety subscales, respectively). Cronbach’s alpha was high for the three subscales in parents of children with ASD: 0.91 for stress, 0.87 for anxiety, 0.94 for depression, and 0.92 for full scale [51]. It has also been validated in the Hong Kong population [52].

*Satisfaction with Life Scale (SWLS)* [53]. The SWLS has five items scored on a 7-point scale (1 = strongly disagree to 7 = strongly agree) measuring participants’ satisfaction with life and has a Cronbach’s alpha for internal consistency of 0.87 and a test-retest correlation of 0.82 [53]. This scale has also been validated in Chinese [54] and Hong Kong populations [55].

*Psychological Empowerment Scale for parents of children with a disability (PES)* [56]. It is a 32-item questionnaire on a 5-point scale (1 = strongly disagree to 5 = strongly agree) with four underlying sub-scales: (a) attitudes of control and competence, (b) cognitive appraisals of critical skills and knowledge, (c) formal participation in organizations, and (d) informal participation in social systems and relationships (57). This scale showed high-reliability coefficients (0.90–0.97) [56].

Parents’ life events will be prompted daily in the EMI/A app, and questions will be modified from the systematic review that summarizes the risk and protective factors of psychological distress [57]. The shortened version of the scale measuring mindfulness and psychological distress will be embedded in EMI/A and prompt out every day for future analysis.

#### Post-trial qualitative interviews

At the completion of the intervention, participants from the intervention group will be invited for a qualitative interview to evaluate the effectiveness of EMI/A-MBI. Participants who consent to take part in the semi-structured interview will be invited to discuss their experiences of using EMI/A-MBI. All interviews will be audio-recorded. After each interview, digitally recorded audio files will be saved and transcribed by the student helper into text. Nvivo 11 [58] will be used for qualitative data analysis. Significant non-verbal and para-linguistic conversations related to participants’ experiences of using EMI/A-MBI will also be noted and recorded. Thematic analysis will be utilized for data analysis, following six steps of thematic analysis, including the familiarity with the data, generating initial codes, searching for themes, reviewing themes, defining and naming themes, and producing the report [59]. The PI and RA will use open- coding to identify relevant content in the transcripts. Then the PI will classify all labeled content into several independent themes showing distinct features of the participants’ feedback. Results will then be discussed and consolidated in panel meetings with other co-investigators.

#### Follow-up and incentive

To minimize the survey effect of EMI on the study outcomes and to assess the long-term impact of EMI/A-MBI, a telephone follow-up to assess the study outcomes will be conducted two months after the completion of the EMI/A-MBI.

The EMI validity largely relies on the participants’ compliance. Therefore, an attractive incentive is needed. All participants will be given a HK$50 gift voucher upon completing the baseline, post-study, and 2-month follow-up surveys. In addition, participants in the EMI group who have successfully completed all EMIs in the 8-week will be given an additional HK$50 gift voucher.

### Confidentiality

#### Ethical consideration and declarations

This trial was approved by the Human Research Ethics Committee of Lingnan University (Reference No.: EC077/2223, approved protocol can be found in S3 File). Written informed consent will be sought and obtained from all research participants (Example consent form can be found in S4 File), and participants have the right to withdraw from the research at any time without penalty.

The entire protocol will be uploaded on clinicaltrialregistration.org for public access. The participant-level data and statistical code will be available upon request to the corresponding author after the completion of the study.

Personal information about potential and enrolled participants will be collected, shared, and maintained in strict confidence following the SPIRIT guidelines. The SPIRIT guidelines will be accomplished through a variety of measures, including obtaining informed consent from participants, using unique study identification numbers to de-identify data, storing data securely with restricted access, and only disclosing information to authorized parties with a legitimate need to know. In addition, participants will be informed of their rights to access their personal information and withdraw at any time. Before, during, and after the trial, the participants’ personal information will be protected by these measures.

### Data analysis

Data analysis will be conducted using STATA 17 [60]. All significance tests were two-sided with a 5% level of significance. Missing data will be calculated using intention-to-treat approach. Participants who failed to answer the prompted questions will be treat as no improvement on the outcomes. The characteristics of the observed data and the missing data will be compared to determine whether there are any systematic differences. If tested that the missing data will be missing not at random, imputation methods, such as multiple imputation (MI) or maximum likelihood estimation (MLE), will be adopted to estimate the missing values based on the observed data and the relationships between variables. Moreover, sensitivity analysis will be adopted to assess the impact of the missing data on the study results and to determine the robustness of the findings. Complete case analysis and multiple imputation will also be conducted as sensitivity analysis. The internal consistency of the constructs for mindfulness, depression, anxiety, stress, and life satisfaction will be assessed with Cronbach’s alpha. In each construct, the PI will sum all items to build the score for that attribute in each participant.

To answer the first and second questions, first of all, the effect size (Heges’ g) of the outcome for both the intervention and control groups will be calculated. Subgroup analysis will be conducted when necessary. Next, linear mixed models will be conducted to compare the effectiveness of the mindfulness intervention between the two treatment groups. Linear mixed models are particularly suitable for analyzing data collected via ecological momentary assessment, as they can account for the nested and repeated nature of the data. The main predictor variable will be the treatment group (intervention vs. control), and the model will also include baseline DASS scores and any relevant demographic variables (e.g., age, gender) as covariates. The linear mixed model will include random intercepts and slopes for each participant to account for individual differences in the baseline scores and the rate of change in scores over time. The treatment group effect will be assessed using a fixed effect, and the model will also include an interaction term between treatment group and time to investigate any differential effects of the intervention over time.

To answer the third question, structural equational modelling will be adopted to examine the pathways of the relationship between daily life events, cognitive appraisal, and psychological distress. Moderation analysis will also be used to explore the effects of mindfulness. The model will be adjusted for the participants’ role of mother or father. Bootstrapping with size 10,000 will be used to estimate the 95% confidence interval of the parameters. After checking data distribution normality, several fit indices will be served as the judgment of the fit of the model. A non-significant chi-square (X^2^) is desired, but the test is sensitive to erroneously reject a correct model when the sample size is not large enough [61]. The Comparative Fit Index (CFI) and the Non-Normal Fit Index (also known as the Tucker-Lewis Index, TLI), ranging from 0.00 to 1.00, with higher values representing better fit, will be adopted [62]. The standardized root-mean-square residual (SRMR) and root mean square error of approximation (RMSEA) will be used to detect model misspecifications, with values below 0.08 considered desirable [62]. The indirect effect of the model will be checked with the Sobel test.

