#### Sample size

The sample size calculation for this study is based on the linear mixed model that will be adopted to answer research questions 1 and 2 based on the repeated ecological momentary assessment data from the intervention and control group and the effect size of 0.29 from previous studies (unpublished manuscript). The R package *sjstas* [44], and *pwr* [45] were used for sample size calculation. The results indicate that a total of 536 participants will be required to detect a significant difference at an alpha level of 0.05 and a power of 80%. Accounting for potential dropouts, we conservatively estimate that 20% of participants may not complete the study. Therefore, we plan to recruit 670 participants (335 in each group).

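### The missing-data rule treats MNAR as testable, answers it with MAR methods, and fills non-response with zero change, which conflicts with the planned mixed model and imputation

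*Protocol article*

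**What the plan says.** All the relevant rules stand in one paragraph of the protocol article, under Data analysis.

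- Non-response: "Participants who failed to answer the prompted questions will be treat as no improvement on the outcomes".
- Diagnosis: "The characteristics of the observed data and the missing data will be compared to determine whether there are any systematic differences".
- Action on the diagnosis: "If tested that the missing data will be missing not at random, imputation methods, such as multiple imputation (MI) or maximum likelihood estimation (MLE", and these methods "will be adopted to estimate the missing values based on the observed data and the relationships between variables".
- Sensitivity: "Complete case analysis and multiple imputation will also be conducted as sensitivity analysis", after a general promise to examine the impact of missing data.

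The next paragraph plans a linear mixed model with random intercepts and slopes, baseline DASS as a covariate and a group-by-time interaction. The paragraph gives no order between the zero-change rule, the imputation step and this model.

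The only missing-data figure in the document is in the Sample size section: 20% dropout overall, not split by arm.

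**The concern.** Three things are wrong as written.

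1. **The diagnosis cannot be made.** Comparing people with and without data can give evidence against missing completely at random. It cannot separate MAR from MNAR, because the difference lies in values nobody has seen.
2. **The remedy contradicts the trigger.** MI and maximum likelihood built on observed data and the relations among variables are valid under MAR. The plan reserves them for the case in which that assumption has been declared false.
3. **The zero-change rule fills in a guess and treats it as data.** Once it is applied, nothing is left for MI or the mixed model to estimate. The filled-in values have no spread, so standard errors understate the uncertainty about actual change. A non-responder who got worse is recorded as unchanged.

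The rule bears on the primary DASS comparison. Both arms receive mindfulness, so both may improve. Fixing non-responders at zero then shifts each arm's mean by an amount that depends on how many are missing there.

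**Working it through.** **The plan's own figure.** 536 / (1 − 0.20) = 670, or 335 per arm. This reproduces the stated target. At 20% dropout, 0.80 × 335 = 268 per arm remain.

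**Inputs.** From the document: effect size 0.29 (Sample size; read here as a standardised difference with SD 1, since the metric is not named), 335 per arm, 20% dropout, two-sided 5% level. Assumed: control improvement 0.30 SD, so app improvement 0.30 + 0.29 = 0.59 SD; the split of missingness by arm; and a true difference that also holds in non-responders.

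**Formulas.** Let p be the missing share and m the mean improvement in an arm.

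- Contrast under zero-filling: (1 − p_app) × m_app − (1 − p_ctl) × m_ctl.
- Variance in an arm after zero-filling: (1 − p) + p(1 − p)m².
- SE: √[(V_app + V_ctl) / 335].
- Power: two-sided normal approximation.

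**Equal missingness, 20%/20%.**

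- Contrast: 0.8 × 0.59 − 0.8 × 0.30 = 0.232.
- Variances: 0.8 + 0.16 × 0.59² = 0.856 and 0.8 + 0.16 × 0.30² = 0.814.
- SE: √(1.670 / 335) = 0.0706. Power is about 91%.
- Completers only, 268 per arm: SE √(2/268) = 0.0864. Power for 0.29 is about 92%.
- No missing data at all: SE √(2/335) = 0.0773. The zero-filled SE is smaller even than this, which shows the false precision.

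**Unequal missingness, app/control.**

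| Split | Contrast (true 0.29) | Power |
|---|---|---|
| 30%/10% | 0.7 × 0.59 − 0.9 × 0.30 = 0.143 | about 52% |
| 10%/30% | 0.9 × 0.59 − 0.7 × 0.30 = 0.321 | not needed: the effect is overstated |

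**No true effect, both arms improving 0.40 SD, 30%/10%.** Contrast: 0.7 × 0.40 − 0.9 × 0.40 = −0.08. With SD held at 1 (SE 0.0773) the rejection rate is about 18%. With the shrunken variance (SE √(1.648/335) = 0.0701) it is about 21%. The nominal rate is 5%. With equal missingness the false contrast is zero.

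**Can the planned comparison detect MNAR?** In a simulation of 400,000 people, baseline was standard normal and outcome was 0.6 × baseline + 0.8 × noise. The log-odds of being missing were −1.6 + 0.8 × baseline (MAR) or −1.6 + 0.8 × outcome (MNAR). About 19% were missing either way. Missing and observed people differed at baseline under both mechanisms, by 0.72 SD under MAR and 0.43 SD under MNAR, so a difference does not tell them apart. Regression imputation from observed data recovered the mean under MAR (error below 0.001 SD) and missed it by about 0.09 SD under MNAR.

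The two-sample formula serves here only to compare scenarios. It does not reproduce the plan's 536, which is a separate matter.

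**The case against.** **The rule is conservative at the only rate the document gives.** This stands. At 20% in both arms the effect is attenuated and power falls by about one percentage point against completers only. With no true effect and equal change in both arms, equal missingness adds no bias. The larger shifts need arm-specific rates that the document does not give.

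**The scope of the rule is unclear.** This also stands. Prompted questions may mean the daily app items only, while the DASS survey goes to both arms at baseline, post-test and follow-up. An unanswered prompt need not be a missing survey score. Yet the Sample size and Data analysis sections tie the primary model to repeated momentary data, and the former says these come from both groups. A reader might infer that the rule acts mainly on the app arm, but the text does not settle that.

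**A reader might infer that the rule hides harm in the app arm**, because "The intervention will be discontinued or modified when participants report feeling more psychological distress". The documents do not support this. That sentence concerns the intervention, not assessment. It is not limited to the app arm, and nothing says surveys end when the app does. An example of strong inflation can be built: with a true difference of 0.15 (improvement 0.45 against 0.30, SD 1), scoring the worst 10% of the app arm alone as unchanged gives 0.28. If both arms lose their worst 10%, the figure is about 0.135 and the inflation is gone.

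**Naming no MNAR sensitivity method is an omission that an SAP may fill.** Agreed, and it is not counted as an error. MI can also be read as only a check on a zero-change primary analysis. The defect is that the order is not stated.

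None of this rescues the MNAR test, the mismatched remedy, or the filling-in of zero change ahead of a model that needs no such step.

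**Conclusion.** The point holds as an error in what the protocol states. MNAR cannot be tested as described, the prescribed response assumes MAR, and the zero-change rule conflicts with the mixed model and MI, understates uncertainty and cannot record worsening among non-responders.

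Its numerical effect is conditional. At 20% missing in both arms, 0.29 becomes about 0.23 and the rule is conservative. Under assumed splits of 30%/10% and 10%/30%, with control improving by 0.30 SD, it becomes about 0.14 or 0.32. With no true effect, 0.40 SD improvement in both arms and a 30%/10% split, there is a false contrast of about 0.08 SD and roughly 18–21% rejection. So the rule is not reliably conservative, but neither can it be said to favour the app or to conceal deterioration there. Direction and size depend on missingness by arm and on what happens to non-responders, which the document does not give.

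**What to change.** - Delete the rule that scores non-responders as unimproved, and the rule that invokes MI or maximum likelihood after an MNAR finding.
- State as primary the likelihood-based linear mixed model that is already planned, on all randomised participants by assigned arm, under an explicit MAR assumption. Use all survey data, including those collected after app use stops.
- Keep the comparison of people with and without data as description only. It should not choose the method.
- For MNAR, use MI by arm with a delta shift (tipping point), allowing values worse than baseline. Keep complete case as supportive only.

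The cost is protocol wording and a little more analysis work. It should be settled before outcome data are seen, because the current text lets a data comparison select the method.
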